### Data Collection

We will use disguised observation [30-34] to collect data. A total of 3 trained observers (undergraduate students, writing their master’s thesis) from the School of Pharmacy, University of Groningen and Utrecht University, the Netherlands, will observe the nurses while they give drugs to inpatients. To prevent nurses adjusting their behavior in the BCMA process while under observation, the observer will be introduced as being on the ward to monitor the performance of the medication distribution system on that ward. The observer will take part in several planned medication administration rounds on that ward and also observe unscheduled medication administrations. The observer will randomly pick a medication administration round with a minimum of 3 rounds every day and a weekly minimum of 18 rounds. During the different rounds, the observer will observe as many different nurses as possible. To prepare for the observation, the observer will study the standard operating procedures or the applicable drug administration procedures of the specific ward and the agreements on the BCMA process of that ward. In practice, the observer will accompany the nurse who administers the medication using the BCMA system and observe the administration of each dose of medication to the patient. The observer will record the nurses’ actions of giving drugs to the patients (according to the forms in Multimedia Appendix 1,Multimedia Appendix 2, and Multimedia Appendix 3). After each observed medication administration round, we will collect a (printed) computer output of the medication for that specific patient, day, and round from the hospital’s electronic patient records. Consequently, we will compare observation records with the prescribed medication on this computer output and with available standard operating procedures of the BCMA process for that specific ward, to identify workarounds and MAEs. We designed an Access database in which we will record the observation data and which we will link to each patient’s prescription and medication data.

If the observer becomes aware of a potentially serious error, the observer will intervene for ethical reasons, but the data will be included in the study.

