### Definitions and Classification

Workarounds are defined as “informal temporary practices for handling exceptions to normal workflow” for that specific ward and are operationalized as deviations from the available protocols [24]. Figure 1 depicts the BCMA workflow and the potential risk factors for workarounds in the BCMA process. We will classify workarounds using a self-developed classification system (Table 2) derived from the system of Koppel et al [26]. Workarounds can be related to patient identification, the scanning process, the alert signals, and other procedures, or can be work related. Allan and Barker [41] defined MAEs as “the administration of a dose of medication that deviates from the prescription as written (or ordered by CPOE) on the patient medication chart, or from standard hospital policy and procedures.” We will compare drug administrations with the doctor’s prescriptions as noted in the CPOE system in the pharmacy database. We will exclude intravenous and nonintravenous preparation errors because these errors are not preventable by BCMA and are thus unlikely to be influenced by workarounds in the BCMA process. We will classify the MAEs using the classification of van den Bemt et al [42] (Table 3). We will divide the number of erroneous medication administrations (containing 1 or more errors) by the number of observed drug administrations plus the number of omissions, thus using the concept of opportunities for errors as in other MAE research [43].

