### Data Monitoring

We will enter all data into an Access database (version 2010, Microsoft Corporation). The basis for the Access database will be the case report forms in Multimedia Appendix 1,Multimedia Appendix 2, and Multimedia Appendix 3. The first (Multimedia Appendix 1) is designed to collect data on potential risk factors for workarounds, the second (Multimedia Appendix 2) is designed to collect data on MAEs, and the third (Multimedia Appendix 3) is designed to collect data on observations of workarounds. These data will be made available to other researchers and editors on request. Data entry errors will be minimized by using multiple choice options and fixed data fields. At the end of the study, 10% of the entered data will be checked by a second researcher. If data entry errors are found, additional portions of 10% of the data will be checked until no errors are found within a portion. Also, a periodic backup of the study database of each hospital will be made and checked for missing data. Access to the research databases will be secured by passwords. Changing the format of the study documentation or study databases will be restricted to the primary investigator. New versions will be distributed from the central study location (the University of Groningen, the Netherlands). Before data analysis, we will lock the final database.

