### Strengths and Limitations

The strength of the Dutch BCMA study is that it will provide quantitative information about workarounds and their possible association with MAEs, as one of the first studies worldwide, to our knowledge. Other strengths are the multicenter design, which enhances its generalizability, and the robust method of data collection by disguised observation.

There are some limitations and considerations, however. An important limitation, in general, is that the use of BCMA cannot prevent all MAEs. For example, BCMA systems will have no influence on the preparation of intravenous and nonintravenous medication. So, although this study will contribute to patient safety, further studies into other ways of preventing MAEs will remain necessary.

Although disguised observation is the best method for data collection in MAE studies, some limitations are associated with this technique. Despite thorough training of the observers, bias may still occur. To overcome observation bias, we considered the use of the work observation method by activity timing [34,48]. This elegant paperless method is used for time- and activity-based observations and is less suitable for observing workarounds and MAEs.

The observations may influence the nurse but, from the literature, we know that this effect (known as Hawthorne effect) [49,50] is small. The observer may also become tired and thus less accurate. How to train observers is not well documented in the literature. Patterson et al [19] performed an observational study in acute and long-term care wards using observers trained in ethnographic observations in complex settings. Other researchers trained nurse students as observers [51]. We will use all possible means, as well as the best possible literature base, to train the students.

We will try to reduce confounding by applying multivariate regression analyses (eg, hospital type, type of ward). However, in this type of observational study design, residual confounding may always remain [52].

Last but not least, we plan to conduct our research on internal medicine and surgical hospital wards. Although these nursing wards cover a broad range of patient categories, our findings cannot be generalized to all patient categories.

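### Workarounds and MAEs come out of one unmasked post-round comparison, so the coding of judgement-based MAEs could be influenced by knowledge of the workaround

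*Protocol article*

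**What the plan says.** Under Data Collection, the observer accompanies the nurse: "The observer will record the nurses’ actions of giving drugs to the patients", using the three appendix forms. After the round, "we will compare observation records with the prescribed medication on this computer output and with available standard operating procedures" of the BCMA process for that ward, with the stated aim "to identify workarounds and MAEs". The disguise described there concerns how the observer is introduced to the nurses.

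Under Definitions and Classification, workarounds are "operationalized as deviations from the available protocols". MAEs are deviations from the prescription "or from standard hospital policy and procedures". The same section then says: "We will compare drug administrations with the doctor’s prescriptions as noted in the CPOE system in the pharmacy database".

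Under Data Monitoring, MAEs and workarounds have separate forms. Appendix 2 is for MAEs, and "the third (Multimedia Appendix 3) is designed to collect data on observations of workarounds".

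Under Strengths and Limitations, the authors concede: "Despite thorough training of the observers, bias may still occur". They go on to discuss another recording method, the Hawthorne effect and observer fatigue. Knowledge of the exposure when the outcome is judged is not mentioned.

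**The concern.** The primary aim is the association between workarounds and MAEs at the level of the single administration. Such an estimate is trustworthy only if an MAE is as likely to be recognised, and as unlikely to be called wrongly, with a workaround as without one. If the person coding the MAE can see that scanning was skipped, a doubtful administration may be read more strictly. Error recognition then differs by exposure, and an association can appear where there is none.

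The planned model would not correct this. The adjustment set (hospital, ward type, day, time schedule, ATC code, number of drugs, route) and the nurse and patient levels deal with confounding and clustering. Outcome misclassification that depends on the exposure is left in the odds ratio.

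**Working it through.** **1. Which steps and comparators are shared**

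| | Workaround (exposure) | MAE (outcome) |
|---|---|---|
| Recorded by | Observer on the round | Observer on the round |
| Form | Appendix 3 | Appendix 2 |
| Identified in | Post-round comparison | The same post-round comparison |
| Main comparator | Ward BCMA procedures | CPOE prescription |
| Further comparator | None stated | Hospital policy and procedures, by definition |

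The forms and main comparators are separate. The recorder, the step as described, and the procedures part of the definitions are shared.

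**2. Which MAE types are exposed**

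Table 3 has seven types. Six can largely be settled against the prescription: omission, unordered drug, dosage form, route, dosage, and time (with a 60-minute rule). Wrong administration technique is the main type that needs judgement. Deviations counted only under the procedures part of the definition also need it.

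**3. Possible size**

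The document gives no detection rates, so the following are assumptions: a true MAE risk p of 10% in both groups (the protocol cites about 10% from prior studies), no false-positive MAEs, and detection probability Se1 with a workaround and Se0 without.

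Observed risks: q1 = p × Se1 and q0 = p × Se0. Odds ratio: OR = [q1/(1 − q1)] / [q0/(1 − q0)].

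- Se 0.90 against 0.75: q1 = 0.090, q0 = 0.075; OR = (0.090/0.910)/(0.075/0.925) = 0.0989/0.0811 = 1.22
- Se 0.90 against 0.80: q1 = 0.090, q0 = 0.080; OR = 0.0989/0.0870 = 1.14
- Se 0.85 against 0.80: q1 = 0.085, q0 = 0.080; OR = 0.0929/0.0870 = 1.07
- Equal Se: OR = 1.00

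The true rate matters little. At the extremes of the pilot range, 0.90 against 0.75 gives (0.018/0.982)/(0.015/0.985) = 1.20 at 2%, and (0.18/0.82)/(0.15/0.85) = 1.24 at 20%.

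**4. Effect on the test**

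With 6000 administrations and the planning assumption of 8% workarounds, there are 480 exposed and 5520 unexposed. Ignoring clustering, a two-sided 5% comparison under 0.90 against 0.80 rejects a true null in about 9% of studies at a true MAE rate of 5%, and in about 13% at 10%.

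**5. A different error mechanism**

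Suppose instead that Se is 0.90 in both groups, but 5% of error-free administrations are wrongly coded as MAEs only where a workaround was seen. At p = 10%, q1 = 0.090 + 0.90 × 0.05 = 0.135 against 0.090, a relative risk of 1.50. At p = 5%, q1 = 0.045 + 0.95 × 0.05 = 0.0925 against 0.045, a relative risk of 2.06. Nothing in the document indicates that this happens. It shows only that false positives would matter more than missed errors.

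**The case against.** The strongest reply is that the article says only that the team will make the comparison. It does not say who codes, in what order, or with which forms in view. A reader might infer that one person codes the MAE straight after seeing a skipped scan and with the hypothesis in mind. The text does not establish this, and the appendix forms and full protocol are not shown. That part of the objection stands. What remains is that the one step the article does describe yields both variables, with nothing separating them.

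Second, MAEs have their own form, their own typology and the prescription as main comparator. This stands for most Table 3 types, so a reader who takes dose or time errors to be as exposed as technique errors goes too far. It does not cover technique, or the procedures part of the definition.

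Third, much of any detection difference may arise at the bedside, where the observer cannot be masked. This also stands. The assumed rates do not split bedside from coding, so the share of the bias that masked coding would remove is unknown.

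Fourth, the observers are trained, examined (pass mark 8 out of 10) and piloted under supervision, and residual observer bias is disclosed. Training should reduce error overall, but it does not make error independent of the exposure.

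**Conclusion.** The point holds as a weakness that can be reduced at modest cost. Workarounds and MAEs are identified in one described comparison without masking, and deviation from procedures appears in both definitions. Knowledge of the workaround could therefore influence MAE coding, mainly for technique and procedure-based errors, and could bias the primary odds ratio. The direction is probably away from 1, on the assumption that a seen workaround prompts stricter scrutiny.

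The OR range of 1.07 to 1.22 rests on assumed detection rates, a true MAE risk of 10%, no true effect and no false positives. It illustrates the mechanism and is not an estimate for this study. A reader might infer that the association will be spurious, or that the bias could account for the planned relative risk of 2. The document supports neither: no detection difference is documented, and only the assumed false-positive scenario comes near that size.

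**What to change.** 1. Derive prescription-based MAEs (omission, unordered drug, dose, form, route, time) by fixed rules from the Access database, which is already planned to link observations with prescription data.
2. Code the remaining judgement-based MAEs from the MAE form, the CPOE printout and the applicable hospital administration procedures other than those for BCMA. Withhold the workaround form. Where feasible, use a trained observer or researcher who did not watch that round. Using the printout alone would drop the procedures part of the adopted definition.
3. Lock the MAE codes before workarounds are coded against the ward procedures.
4. Because enrollment is complete, do this as masked re-coding of the stored records before database lock. The article reports analysis as under way, so if the lock has passed, keep the masked codes beside the locked ones and report both.
5. Report a sensitivity analysis of the primary model limited to prescription-based MAEs.
6. State as a limitation that what was noticed or noted at the bedside could still depend on the workaround.

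The cost is some re-coding and some queries to the original observer. Existing forms and data suffice, provided the stored MAE records hold the needed fields (the appendix forms are not shown) and a second trained coder is still available. The sensitivity analysis in item 5 needs no judgement-based re-coding.

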### Training of the Observers

We will train our observers by having them study relevant literature on observational techniques [19,30,34-40], perform practical observations in a nonparticipating hospital under the supervision of the research team, and complete a written theoretical exam. The observers will have to pass the exam scoring 8 out of 10 points, having two chances to pass the exam. In case of a second failure, he or she will not be able to observe. Each observer will do pilot observations in a participating hospital, supervised by 1 of the researchers, for 1 week on the wards, to become familiar with the BCMA process. Pilot observations will be discussed with the research team. These observations are meant as a final training of the observer. Pilot data will be discarded.

### Definitions and Classification

Workarounds are defined as “informal temporary practices for handling exceptions to normal workflow” for that specific ward and are operationalized as deviations from the available protocols [24]. Figure 1 depicts the BCMA workflow and the potential risk factors for workarounds in the BCMA process. We will classify workarounds using a self-developed classification system (Table 2) derived from the system of Koppel et al [26]. Workarounds can be related to patient identification, the scanning process, the alert signals, and other procedures, or can be work related. Allan and Barker [41] defined MAEs as “the administration of a dose of medication that deviates from the prescription as written (or ordered by CPOE) on the patient medication chart, or from standard hospital policy and procedures.” We will compare drug administrations with the doctor’s prescriptions as noted in the CPOE system in the pharmacy database. We will exclude intravenous and nonintravenous preparation errors because these errors are not preventable by BCMA and are thus unlikely to be influenced by workarounds in the BCMA process. We will classify the MAEs using the classification of van den Bemt et al [42] (Table 3). We will divide the number of erroneous medication administrations (containing 1 or more errors) by the number of observed drug administrations plus the number of omissions, thus using the concept of opportunities for errors as in other MAE research [43].

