**Figure 1 figure1:**
[figure not shown]
Flowchart of the bar code-assisted medication administration (BCMA) process in hospitals.

**Table 2 table2:** Classification of workarounds in the bar code-assisted medication administration process^a^.

Workaround type	Example workaround
Procedure related: standard operating procedure, or procedure unclear or unknown	Nothing scanned
Patient related: no patient wristband or patient not in the room	Bed scanned, or loose wristband scanned, patient unscanned
Medication related: medication not bar coded	Unscanned, unidentified medication given
Nurse related: nurse disturbed	Nurse forgets patient or gives medication twice
Computer or scanner related: computer or scanner down or broken	Signals or alerts unseen, unscanned medication given
Other workarounds	Medication scanned for multiple patients; half tablets scanned as full dose

^a^Derived from Koppel et al [26].

**Table 3 table3:** The most basic characterization of medication administration errors (MAEs)^a^.

MAE type	Example MAE
Omission	Drug prescribed, but not administered
Unordered drug administration	Drug administered, but not prescribed
Wrong dosage form	Drug dosage form administered to the patient deviating from prescribed dosage form: solution as an alternative to tablet
Wrong route of administration	Drug given by a wrong route of administration: oral liquid administered intravenously
Wrong administration technique	Drug administered using a wrong technique: intravenous push instead of intravenous infusion
Wrong dosage	Drug dosage too high or low: 20 mg instead of 20 μg
Wrong time of administration	Drug given at least 60 minutes too early or too late

^a^From van den Bemt et al [42].

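### One Table 2 workaround type is itself a medication administration error under Table 3, so part of the primary odds ratio is built in by definition

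*Protocol article*

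**What the plan says.** **Exposure.** Under Definitions and Classification, workarounds are "operationalized as deviations from the available protocols" and are sorted by Table 2. The example in its nurse-related row is "Nurse forgets patient or gives medication twice".

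**Outcome.** The same section defines an MAE as a dose that "deviates from the prescription as written (or ordered by CPOE) on the patient medication chart, or from standard hospital policy and procedures". It then says that administrations are compared with the CPOE prescription and classified by Table 3. Table 3 includes omission ("Drug prescribed, but not administered"), unordered drug ("Drug administered, but not prescribed") and a dosage that is too high or too low. The only stated exclusion is preparation errors.

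**Denominator.** Erroneous administrations are divided "by the number of observed drug administrations plus the number of omissions", so each omitted dose is a unit that counts as an error.

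**Ascertainment.** Under Data Collection, one observation record is compared with the prescription output and "with available standard operating procedures of the BCMA process for that specific ward, to identify workarounds and MAEs".

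**Analysis.** Under Statistical Analysis, the primary model is a multilevel logistic regression of MAE on workarounds (none, 1, 2, or 3 and more). The adjusted model adds hospital, ward type, day, round time, ATC code, number of drugs and route. Nothing says that an event may count on one side only.

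**The concern.** The primary question is whether administrations with a workaround contain errors more often than those without. That can be learned only if a record's workaround status can be set without knowing whether an error occurred. For the nurse-related row of Table 2 it cannot. Coding a patient as forgotten already asserts an omission, and coding a dose as given twice already asserts an unordered drug or a wrong dosage. For these records the probability of an MAE given a workaround is 1, whatever happens on the ward.

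Adjustment does not help, because none of the listed covariates can separate two labels given to one event. Because omitted doses are units of analysis, one forgotten patient with several drugs due can also add several double-positive records. The result is meant to guide error reduction, and an odds ratio set partly by coding is a poor basis for that.

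**Working it through.** **1. The two tables side by side**

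| Event in Table 2 (exposure) | Table 3 type (outcome) | MAE certain once coded? |
|---|---|---|
| Patient forgotten | Omission | Yes |
| Medication given twice | Unordered drug or wrong dosage | Yes |
| Nothing scanned; bed or loose wristband scanned | None by itself | No |

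The clear overlap is in the nurse-related row. Most other rows describe process breaches that may or may not end in an error.

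**2. Inputs**

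From Sample Size Calculation: 8% of administrations with a workaround, relative risk 2, alpha .05, power 0.9, 1500 administrations per hospital, MAE rate about 10% in prior studies, pilot rates 2%, 4%, 5% and 20%. From the Abstract: 6000 administrations, hence 0.08 × 6000 = 480 with a workaround. Not in the article, so assumed: the overlap share f, the fraction of workaround records that are MAEs by definition.

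**3. The plan's own figure**

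With an overall MAE rate of 10%, the rate without a workaround is p0 = 0.10/(0.92 + 0.08 × 2) = 0.10/1.08 = 9.26%, and with a workaround 18.52%. The two-proportion formula with pooled variance and allocation 0.92/0.08 = 11.5 gives 123 exposed and 1538 in total with one-sided alpha, and 1850 two-sided. So 1500 is reproduced to within 3%, but only one-sided and with independent observations. This point does not dispute that figure; it serves to fix a plausible p0.

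**4. Overlap with no true effect**

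The observed risk with a workaround is p1 = f + (1 − f)p0. Setting p1 = 2p0 gives f = p0/(1 − p0):

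- p0 = 10%: 0.10/0.90 = 11.1%
- p0 = 9.26%: 0.0926/0.9074 = 10.2%, about 49 of 480 records
- p0 = 5%: 0.05/0.95 = 5.3%
- p0 = 2%: 0.02/0.98 = 2.0%

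Odds ratio from overlap alone, [p1/(1 − p1)]/[p0/(1 − p0)]:

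| f | p0 = 2% | p0 = 5% | p0 = 9.26% |
|---|---|---|---|
| 1% | 1.51 | 1.20 | 1.11 |
| 2% | 2.02 | 1.41 | 1.22 |
| 5% | 3.63 | 2.05 | 1.57 |
| 10% | 6.56 | 3.22 | 2.20 |
| 20% | 13.5 | 6.00 | 3.70 |

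At p0 = 9.26% and f = 5% (24 of 480 records), a two-sided 5% test on 6000 records is significant with probability 0.865 although no association exists. This ignores clustering and treats workaround as yes or no rather than in four categories.

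**5. Overlap with a true relative risk of 2**

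At p0 = 9.26% the true odds ratio is 2.23. With p1 = f + (1 − f) × 2p0 it becomes 2.35 at f = 1%, 2.86 at 5% and 3.56 at 10%.

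**6. What recoding does**

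Take no true effect, p0 = 9.26% and f = 10% (48 records). If the 48 records are left out, the odds ratio is 1.00. If they only lose the workaround code and move to the reference group, the exposed group has 432 records at 9.26% (odds 0.102). The reference group then has 5520 × 0.0926 + 48 ≈ 559 errors in 5568 (10.04%, odds 0.112). The odds ratio is 0.102/0.112 ≈ 0.91.

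**The case against.** **The shared yardstick.** A reader might infer that exposure and outcome are measured against the same procedures throughout, because the MAE definition ends "or from standard hospital policy and procedures". The article does not support this as a main argument. That wording belongs to a quoted literature definition, and the following text narrows it to comparison with the CPOE prescription and the Table 3 types, none of which is a scanning or identification breach. The Data Collection sentence can also be read as prescription output for MAEs and ward procedures for workarounds. This stands, so the shared wording is secondary. It does not rescue the Table 2 row, because omission, unordered drug and wrong dosage are Table 3 types.

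**Omissions in general.** A reader might also infer that every omitted dose is either exposed by definition or always unexposed, so that its coding alone sets the odds ratio. Table 1 contradicts both halves. In Hospitals 2 and 3, a dose not given to an absent or sleeping patient follows the listed procedure, so it need not be a workaround. In all four hospitals a patient is selected per round, so an identification workaround can be seen even when a dose is then omitted. Only omissions from a forgotten patient are caught.

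**Scale and forms.** The overlap is one example in one of six categories, its share is unknown, and the observation forms in the appendices are not shown and might hold a coding rule. The first two points limit what can be said about size. The third does not remove the conflict: Table 2 as published puts these events in the exposure.

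**Association only.** The stated aim is association, not cause. But an association fixed by definition says nothing about practice under either reading.

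**Conclusion.** The concern holds in a limited form. As written, Table 2 and Table 3 place the same events in the exposure and the outcome, and the primary model has no rule to separate them. The direction is certain: counting them on both sides raises the odds ratio. The size cannot be computed from the article. Over an assumed overlap of 1% to 20% of workarounds and no true effect, the built-in odds ratio runs from 1.11 to 3.70 at a 9.26% MAE rate without a workaround, and from 1.51 to 13.5 at 2%. These figures assume independent records and a yes-or-no exposure. They show how small an overlap would matter; they do not predict this study's bias.

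It does not follow that most workarounds are errors by definition, or that the primary model must be restricted to administered doses. That restriction would change the outcome and drop an error type that workarounds could genuinely cause, so it belongs in a sensitivity analysis.

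**What to change.** 1. Remove the forgotten-patient and double-dose example from the Table 2 exposure classification and count these events only as MAEs. For such records, take workaround status only from separately observed process steps: patient identification, scanning and alerts.
2. State that, for the primary association, an MAE is a deviation from the CPOE prescription of a Table 3 type, so that a procedural breach alone is not an MAE. This mostly makes explicit what the section already implies.
3. Keep the opportunities-for-error denominator. Add a sensitivity analysis that excludes records whose exposure cannot be observed apart from the error (forgotten-patient omissions and double doses), or one limited to administered doses with omissions modelled separately.

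**Cost.** No new data collection should be needed, since Data Monitoring describes separate forms for MAEs and workarounds, provided those forms recorded the process steps. There will be somewhat fewer exposed records and a smaller odds ratio. Step 1 alone can overcorrect: if the recoded records simply join the reference group, the odds ratio falls slightly below 1 with no true effect (about 0.91 in the example above). Step 3 is there for that reason.
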